#### 3.5.2.1 Adverse Events

Information regarding adverse events will be collected and recorded on the Adverse Events case report form. An adverse event is any undesirable sign symptom or medical condition occurring after the subject is enrolled in the study, whether considered drug-related or not. Medical conditions/diseases present before starting study drug are only considered adverse events if they worsened after starting study drug. Study drug includes any drug(s) under evaluation in the study, including reference drug(s), placebo, or any other drug required by the protocol.

Adverse events, whether volunteered by the subject, discovered during general questioning by the investigator, or detected through physical examination, laboratory tests or other means will be recorded on the Adverse Event case report form and followed carefully until they resolve. Abnormal laboratory values or test results should not generally be considered adverse events, unless they induce clinical signs or symptoms or require therapeutic intervention, when they should be recorded on the Adverse Events case report form using an appropriate diagnostic description.

As far as possible, each adverse event will also be described by:

- its duration (start and end dates),
- the severity grade (mild, moderate, severe),
- its relationship to the study drug (suspected / not suspected),
- the action(s) taken

Examples of the severity grade, relationship to study drug and actions taken, as presented in the case report form are provided in **section 6.3: Instruction for completing Adverse Event case report forms**.

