### 3.3.3 Interruption or Discontinuation of Treatment

Before interrupting or discontinuing study drug, the investigator must contact the sponsor or designee (except in the case of an emergency) to discuss the proposed reason. It will be documented whether or not each subject completed the clinical study. If any subject's study treatment or observations were discontinued, the reason will be recorded. Reasons that a subject may discontinue participation in this clinical study may be one or more of the following:

- Adverse event(s)
- Abnormal laboratory value(s)
  - Hemoglobin: decrease below 9.0 gm/dL
  - AST:  $\geq 3 \times$  ULN (upper limit of normal)
  - ALT:  $\geq 3 \times$  ULN
  - LDH:  $\geq 3 \times$  ULN
  - Alkaline Phosphatase:  $\geq 2 \times$  ULN
  - Triglyceride:  $\geq 1000$  mg/L
  - Creatinine:  $>2$  mg/dL
- **Any fasting glucose  $>300$  mg/dL and/or any HbA1c value of  $>12\%$  in spite of ad lib adjustments to oral hypoglycemic agents and/or insulin dosage.**
- Subject withdrew consent
- Lack of compliance to protocol requirements and/or procedures
- Lost to follow-up

- Administrative deviations which preclude satisfactory completion of protocol assessments

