#### 4.1.9 Strategy for Statistical Analysis

The safety population is defined as all subjects who were randomized and received at least one dose of study medication (1 mg TH9507, 2 mg TH9507, or placebo) during the course of the trial. This is the primary population for analysis.

The change from baseline values for biochemical laboratory parameters (secondary endpoints) will be analyzed using analysis of variance techniques (ANOVA) which focus on the between (different regimens) and within (same regimen) comparisons of these measurements over time, with center and insulin use group included as fixed effects. Analyses may be conducted as repeated measures analyses or individual analyses of specific study visits.

Glucose values will be obtained at home four times per day using a standardized glucose meter. Subjects will record glucose values in their diary. Glucose values, downloaded electronically from the glucose meters, will be used for statistical analysis.

The assessment of safety will be based mainly on the frequency of adverse events and on the number of laboratory values that fall outside of predetermined ranges. Other safety data (e.g. vital signs, special tests) will be considered as appropriate.

Adverse events will be summarized by presenting, for each treatment group, the number and percentage of subjects having any adverse event, having an adverse event in each body system and having each individual adverse event. Any other information collected (e.g. severity or relatedness to study medication) will be used to categorize the adverse event data as appropriate.

Laboratory data will be summarized by presenting shift tables using extended normal ranges (baseline to most extreme post-baseline value) by presenting summary statistics of raw data and change from baseline values (means, medians, standard deviations, ranges) and by flagging of notable values in data listings.

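### The adverse event definition does not cover stopping study drug, so an asymptomatic, untreated laboratory stop can be missing from the adverse event frequency

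*Protocol*

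**What the plan says.** Three parts of the protocol bear on this.

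- **AE definition (section 3.5.2.1).** "Abnormal laboratory values or test results should not generally be considered adverse events, unless they induce clinical signs or symptoms or require therapeutic intervention". Where one of those conditions is met, the instruction is explicit: "when they should be recorded on the Adverse Events case report form using an appropriate diagnostic description". The same section has AEs followed until they resolve and, as far as possible, described by duration, severity, relationship to study drug and action taken.
- **Discontinuation reasons (section 3.3.3).** The list is permissive and allows several reasons for one subject: "Reasons that a subject may discontinue participation in this clinical study may be one or more of the following". Adverse events are one bullet. Abnormal laboratory values are another, with limits for hemoglobin, AST, ALT, LDH, alkaline phosphatase, triglyceride and creatinine. These limits are purely numeric, for example "Hemoglobin: decrease below 9.0 gm/dL". A further bullet covers fasting glucose and HbA1c, but only "in spite of ad lib adjustments to oral hypoglycemic agents and/or insulin dosage". For every stop, "If any subject's study treatment or observations were discontinued, the reason will be recorded".
- **Safety analysis (section 4.1.9).** "The assessment of safety will be based mainly on the frequency of adverse events", and the same sentence goes on to name the number of out-of-range laboratory values as the second main basis. AEs are summarized as the number and percentage of subjects in each group with any AE, with an AE in each body system, and with each individual AE. Laboratory data get summary statistics, shift tables to the worst later value, and flags on notable values in listings.

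**The concern.** The primary objective is safety. A laboratory abnormality serious enough to end treatment is an event whose grade and suspected cause one would want on file. Under the AE definition, what makes a laboratory value an AE is symptoms or treatment; its consequence for study drug plays no part. A subject stopped on a numeric limit who feels well and receives no treatment meets neither condition.

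Two things are at stake. The AE table can understate treatment-ending laboratory toxicity. In addition, the assessments attached to AE status may never be collected for these subjects. The second loss is the more serious because it arises at data collection: a later analysis plan can retabulate values and disposition, but it cannot supply a relatedness judgement that nobody was asked to make.

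**Working it through.** The plan states no figure on this point, so there is none to reproduce. The check is a cross-reading, followed by simple arithmetic for scale.

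**Step 1: apply the AE definition to each kind of stop in section 3.3.3.**

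| Stop | Symptoms or treatment? | AE under 3.5.2.1? |
|---|---|---|
| Laboratory limit reached, with symptoms | Yes | Yes |
| Laboratory limit reached, with treatment given for it | Yes | Yes |
| Fasting glucose or HbA1c limit | Treatment adjustment is presupposed | Normally yes |
| AST, ALT, LDH, alkaline phosphatase, creatinine or hemoglobin limit, asymptomatic and untreated | No | Not required |

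Only the last row falls through. The numeric limits carry no symptom or treatment condition, so that row is possible under the text.

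**Step 2: trace where a last-row event appears under section 4.1.9.**

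- AE frequency (any AE, body system, individual AE): can be absent.
- Count of out-of-range laboratory values: present, although a treatment-ending value adds one to the count, as a lesser out-of-range value does.
- Shift table: present if it is the subject's worst value, but the table does not show that treatment ended because of it.
- Listings: flagged if notable.
- Disposition: the reason is recorded under section 3.3.3.
- Severity, relatedness, follow-up to resolution: not called for, because section 3.5.2.1 attaches these to AEs.

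**Step 3: scale.** Inputs: 15 subjects randomized per group (section 3.3.1), all assumed dosed and so in the safety population. If k subjects in an arm have such a stop and no AE record for it, the largest change in that arm's AE incidence is k/15:

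- k = 1: 1/15 = 6.7 percentage points
- k = 2: 2/15 = 13.3 percentage points
- k = 3: 3/15 = 20.0 percentage points

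These are upper bounds for the any-AE figure: a subject with another recorded AE is already counted, so the change from that subject is zero. The full 1/15 applies to the line for the individual event. The values of k are illustrative, since the protocol gives no expected rate of laboratory stops.

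**The case against.** The strongest reply is that little is hidden. The definition says such values are not generally AEs, which leaves room for judgement, and withdrawal of study drug might itself be read as a therapeutic intervention. Stops with symptoms or treatment are AEs, and the glycemic stop, the one closest to this trial's question, normally qualifies. Out-of-range values are a main safety basis on an equal footing with AEs, the shift tables use each subject's worst value, and every discontinuation reason is recorded. The two stop bullets are not mutually exclusive, so one subject can have both reasons. Section 3.5.2.1 also refers to form instructions in section 6.3, which are not in the text at hand and might settle the matter.

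Most of this stands, and it rules out three stronger readings.

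- *That drug-stopping laboratory toxicity drops out of the safety assessment.* It does not; it stays in the laboratory summaries and the disposition data.
- *That a table of AEs leading to discontinuation would show 0% instead of 13.3% after two such stops.* Section 4.1.9 specifies no such table, and how discontinuations are tabulated may properly be left to the analysis plan.
- *That the rule makes TH9507 look safer.* It applies equally to placebo under blinding, so a bias toward TH9507 needs more such stops on active drug.

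The reply does not close the gap itself. Neither the AE definition nor the stop list says whether stopping drug counts as intervention, so sites may classify the same asymptomatic ALT stop differently. The laboratory summaries carry no relatedness judgement. Nothing is concluded here from the absence of section 6.3.

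**Conclusion.** The point holds in a limited form. On the natural reading of sections 3.3.3 and 3.5.2.1, an asymptomatic, untreated laboratory abnormality that ends treatment need not be recorded as an AE. It can then be missing from one of the two main safety bases and carry no severity grade, relatedness assessment or required follow-up to resolution. It remains visible elsewhere in the safety data.

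The size is at most 6.7 percentage points of an arm's AE incidence per such subject, and zero for the any-AE figure where the subject has another AE. The direction of any between-arm distortion is unknown in advance. The conclusion assumes that withdrawal of study drug is not itself a therapeutic intervention, which the available text leaves undefined, and that 15 subjects per arm are dosed. It is a worthwhile and inexpensive correction to a data-collection rule, not a defect that undermines the safety analysis.

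**What to change.** Reconcile sections 3.3.3 and 3.5.2.1. To the conditions under which an abnormal laboratory value is recorded as an AE, add: *or lead to interruption or discontinuation of study drug*. Make the AE form instructions agree. Leave every laboratory limit and every discontinuation rule unchanged.

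The cost is one clause and the matching form text. The downside is slightly higher AE counts. The gain is that treatment-ending laboratory events are recorded in the same way at every site, with severity, relatedness and follow-up collected while that can still be done.

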#### 3.5.2.2 Serious adverse events

Information regarding serious adverse events will be collected and recorded on the Serious Adverse Event (SAE) Report Form. A serious adverse event is defined as any untoward medical occurrence that occurs at any dose and:

- results in death,
- is life-threatening,
- requires inpatient hospitalization or prolongation of existing hospitalization,

- results in persistent or significant disability / incapacity, or
- is a congenital anomaly/birth defect in the offspring of a subject who received study drug.

Important medical events that may not be immediately life-threatening or result in death or hospitalization may be considered an SAE when, based upon appropriate medical judgement, they may jeopardize the subject or may require medical or surgical intervention to prevent one of the outcomes listed in the definition above. Examples of such medical events include allergic bronchospasm requiring intensive treatment in an emergency room or at home, blood dyscrasias, or convulsions that do not result in inpatient hospitalization, or the development of drug dependency or drug abuse.

Any serious adverse event occurring after a subject has signed the informed consent form and until four (4) weeks after the stopping study drug must be reported by the investigator to Theratechnologies or designee within 24 hours of learning of its occurrence, even if not seeming to be drug-related. Follow-up information about a previously reported serious adverse event must also be reported to Theratechnologies or designee within 24 hours of receiving it. The investigator should send the completed Serious Adverse Event Report Form by fax to the local representative responsible (**see Section 6.1: Instructions for rapid notification of serious adverse events**).

### 3.5.2.3 Laboratory Evaluations

Approved laboratories will be used for all assays of TH9507 antibody, IGF-1, IGFBP-1, IGFBP-3, glucose, insulin, insulin antibody, hematology analytes, blood chemistry analytes, and urinalysis. Names, addresses and information concerning sample collections and shipment will be provided separately.

#### 3.5.2.3.1 Hematology

Hemoglobin, hematocrit, platelet count, WBC count, RBC count, and differential.

#### 3.5.2.3.2 Blood Chemistry

AST, ALT, alkaline phosphatase, total bilirubin, creatine phosphokinase (CPK), lactate dehydrogenase (LDH), creatinine, urea, amylase, lipase, uric acid, glucose, cholesterol, LDL, HDL, triglycerides, sodium, potassium, calcium, chloride, protein, albumin.

#### 3.5.2.3.3 Urinalysis

Specific gravity, pH, leukocytes, protein, glucose, ketones, bilirubin, RBCs, nitrites, urobilinogen.

#### 3.5.2.3.4 24-Hour Quantitative Urine Tests

Albumin, creatinine, nitrogen, and total urine volume

#### 3.5.2.3.5 Special Tests

HbA1c, insulin and TH9507 antibodies

#### 3.5.2.3.6 Oral Glucose Tolerance Test (OGTT) with paired glucose and insulin levels

Blood glucose and insulin will be measured at 0 minutes (prior to ingestion of glucose), 30 minutes, 1, 1.5, 2, 2.5, and 3 hours. For these determinations, oral sulfonylureas, insulin, and other insulin secretagogues must be withheld on the morning of the OGTT. Insulin sensitizers need not be withheld at such times.

#### 3.5.2.3.7 Home Blood Glucose

Home blood glucose will be obtained 4 times per day (before breakfast, lunch, and dinner, and at bedtime) using a standard blood glucose meter. The glucose values will be downloaded into a computerized recall system. Subjects will be instructed to record the glucose values in their diaries **and to call the clinic for any glucose value that is >250 mg/dL..** Subjects will be instructed to maintain a consistent meal schedule throughout the study.

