- Obtain body weight.

- Obtain vital signs (BP, RR, PR).
- Perform physical/neurological examinations.
- Review/dispense diary. Subjects should be at least 90% compliant with the diary and diet in order to continue participation in the study.
- Replenish boxes of strips and lancets, if necessary
- Download home glucose readings from 14-day lead-in period.
- Instruct the subjects to call the clinic for any home blood glucose value that is >250 mg/dL.
- Dietician interview and assessment – caloric intake assessment, skin thickness (Harpenden), waist/hip measurements, and body fat mass (Lange).
- Collect 24-hour urine for creatinine and nitrogen.
- Obtain blood (fasting) for laboratory tests – IGF-1, IGFBP-1, IGFBP-3, sera for antibodies to insulin and TH9507, lipid profile, hematology, chemistry, HbA1c
- Perform oral 3-hr GTT with 75Gm Glucose (Glucola).
- Obtain blood for insulin and glucose levels every 30 minutes during OGTT.
- Assign randomized study treatment to subject.
- Administer first dose of blinded study drug in clinic at approximately noon.
- Dispense study drug supply for one week (8 doses).
- Instruct the subject to collect urine the day before the scheduled visit (starting at 6AM) until the morning (6AM) of the clinic visit.
- Schedule Visit 4 to occur 6-8 days following Visit 3.

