#### VISIT 4: (Week 1 ± 1 day; Treatment Period)

- Assess adverse events.
- Review concomitant medications.
- Return all used and unused study drugs.
- Obtain body weight.
- Obtain vital signs (BP, RR, PR).
- Review/dispense diary.
- Download home glucose readings from previous 6-8 days.
- Replenish boxes of strips and lancets, if necessary.
- Collect 24-hour urine for creatinine and nitrogen.
- Obtain blood (fasting) for laboratory tests – IGF-1, IGFBP-1, IGFBP-3, lipid profile, hematology, chemistry.
- Perform oral 3-hr GTT with 75Gm Glucose (Glucola).
- Obtain blood for insulin and glucose levels every 30 minutes during OGTT.
- Administer blinded study drug while in clinic at approximately noon.
- Dispense study drug supply for three (3) weeks (24 doses).

- **Remind the subjects to call the clinic for any home blood glucose value that is >250 mg/dL.**
- Instruct the subject to withhold oral sulfonylurea, insulin, and other insulin secretagogues but he/she may take oral non-sulfonylurea hypoglycemic medication (if oral insulin sensitizer) in the morning of Visit 4.
- Instruct the subject to collect urine the day before the scheduled visit (starting at 6AM) until the morning (6AM) of the clinic visit.
- Schedule Visit 5 to occur 19-23 days after Visit 4.

VISIT 5 and VISIT 6: (Week 4  $\pm$  2 days and Week 8  $\pm$  3 days, Treatment period)

- Assess adverse events.
- Review concomitant medications.
- Return all used and unused study drugs.
- Obtain body weight.
- Obtain vital signs (BP, RR, PR).
- Dietician interview and assessment – caloric intake assessment, skin thickness (Harpenden) , body fat mass (Lange); and waist/hip measurements.
- Review/dispense diary.
- Download home glucose readings for the period since the previous visit.
- Collect 24-hour urine for creatinine and nitrogen.
- Obtain blood for laboratory tests – IGF-1, IGFBP-1, IGFBP-3, lipid profile, hematology, chemistry, HbA1C.
- Perform oral 3-hr GTT with 75Gm Glucose (Glucola).
- Obtain blood for insulin and glucose levels every 30 minutes during OGTT.
- Administer daily dose of blinded study drug in clinic at approximately noon.
- Dispense study drug supply sufficient for four weeks (32 doses).
- Replenish boxes of strips and lancets, if necessary
- **Remind the subjects to call the clinic for any home blood glucose value that is >250 mg/dL.**

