- Instruct the subject to withhold oral sulfonylurea, insulin, and other insulin secretagogues but he/she may take oral non-sulfonylurea hypoglycemic medication (if oral insulin sensitizer) in the morning of Visit 6 and Visit 7.
- Instruct the subject to collect urine the day before the scheduled visit (starting at 6AM) until the morning (6AM) of the clinic visit.
- Schedule Visit 6 to occur 25-31 days following Visit 5, OR
- Schedule Visit 7 to occur 25-31 days following Visit 6.

VISIT 7: (Week 12  $\pm$  3 days)

- Assess adverse events.
- Review concomitant medications.

- Return all used and unused study drugs.
- Obtain body weight.
- Obtain vital signs (BP, RR, PR).
- Determine body mass index.
- Perform funduscopy with dilation by optometrist or ophthalmologist (may be performed within 5 days of date of Visit 7).
- Perform physical/neurological examinations (including examination for diabetic sensory neuropathy).
- Review/dispense diary.
- Download home glucose readings from previous 4 weeks.
- Dietician interview and assessment – caloric intake assessment, skin thickness (Harpender), waist/hip measurements, and body fat mass (Lange).
- Collect 24-hour urine for creatinine and nitrogen.
- Obtain blood (fasting) for laboratory tests – IGF-1, IGFBP-1, IGFBP-3, serum for TH9507 antibody, lipid profile, hematology, chemistry, HbA1C.
- Perform oral 3-hr GTT with 75Gm Glucose (Glucola).
- Obtain blood for insulin and glucose levels every 30 minutes during OGTT
- **Remind the subjects to call the clinic for any home blood glucose value that is >250 mg/dL.**
- **Investigator completes global assessment of diabetes control**
- Replenish boxes of strips and lancets, if necessary
- Subject receives NO STUDY DRUG AT THIS VISIT.
- Schedule Visit 8 (Post-treatment Visit) to occur 25-31 days following Visit 7.

VISIT 8: (Week 16 ± 3 days; Follow-up Visit; 16 weeks after randomization; 4 weeks post-treatment)

- Assess adverse events.
- Review concomitant medications
- Obtain body weight.
- Obtain vital signs (BP, RR, PR).
- Obtain blood for laboratory tests (hematology; blood chemistry; lipid profile)
- Collect urine for urinalysis.
- Schedule mammography (for females) and prostate examination/PSA (for males).
- Dietician interview and assessment – caloric intake assessment, skin thickness (Harpender) , body fat mass (Lange), and waist/hip measurements.
- Review diary.
- Download home glucose readings for the period since Visit 7.

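### Subjects are told to call between visits only for home glucose above 250 mg/dL; a hypoglycemic episode should also trigger a call

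*Protocol*

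**What the plan says.** Section 3.5.2.3.7 sets the frequency of home testing: "Home blood glucose will be obtained 4 times per day (before breakfast, lunch, and dinner, and at bedtime". Subjects write the values in a diary and are told "to call the clinic for any glucose value that is >250 mg/dL".

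The visit lists in Section 3.5.1 repeat the call rule. At Visit 3: "Instruct the subjects to call the clinic for any home blood glucose value that is >250 mg/dL". At Visit 4: "Remind the subjects to call the clinic for any home blood glucose value that is >250 mg/dL". The shared list for Visits 5 and 6 and the Visit 7 list carry the same reminder. That makes five places, each with the same single threshold.

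In the visible text, hypoglycemia appears as a diary item (Section 3.2 and the Visit 2 list) and in exclusion criterion 8 (Section 3.3.2). No low-glucose value is given anywhere, and no visible sentence asks for a call after a low reading or a hypoglycemic episode.

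**The concern.** The primary objective is safety in treated type 2 diabetics. The protocol already has a diary and a downloaded meter, and it adds a call rule so that the site hears of a high reading without waiting for a visit. It gives the site no matching notice of a low.

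At stake is how soon an investigator can react, for example by cutting back a sulfonylurea or insulin dose. There is also a conditional effect on reporting. Under Section 3.5.2.2 the 24-hour report to the sponsor runs from the time the investigator learns of a serious event. If a low met the definition of serious, late notice to the site would also delay that report.

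**Working it through.** The protocol has no figure of its own to reproduce here. The check compares its provisions and reads the intervals from the visit windows.

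**1. Are lows foreseeable on the protocol's own terms?**
- Inclusion criterion 4: every subject takes oral hypoglycemics, with or without insulin.
- Section 3.4.4: doses of these drugs may be changed during the trial at the investigator's discretion. Section 3.3.3 also refers to such adjustments. A call about a high reading can lead to a dose increase.
- Section 1: a GRF analogue was associated with enhanced insulin sensitivity in males. With glucose-lowering doses unchanged, that would tend to lower glucose.

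**2. Does eligibility remove subjects prone to lows?** Exclusion criterion 8 has two limbs.
- Episode count: two or more severe episodes in the past 6 months exclude, as does more than one in the lead-in.
- Severity of consequence: any hospitalization or emergency room visit for poor glycemic control excludes, in either period.

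A subject with one severe episode in the past 6 months, or one in the lead-in, is therefore not excluded by this criterion, provided the episode did not lead to such a hospitalization or visit.

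**3. When does the site see a low?** Diary review, meter download and adverse event assessment are listed at visits. The scheduled intervals are:

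| Interval | Source | Days |
|---|---|---|
| Visit 3 to 4 | "Schedule Visit 4 to occur 6-8 days following Visit 3" | 6 to 8 |
| Visit 4 to 5 | "Schedule Visit 5 to occur 19-23 days after Visit 4" | 19 to 23 |
| Visit 5 to 6 | Visits 5/6 list | 25 to 31 |
| Visit 6 to 7 | "Schedule Visit 7 to occur 25-31 days following Visit 6" | 25 to 31 |
| Visit 7 to 8 (off study drug) | "Schedule Visit 8 (Post-treatment Visit) to occur 25-31 days following Visit 7" | 25 to 31 |

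A low just after a visit could thus wait up to 31 days for its scheduled review, unless the subject calls unprompted or the site makes contact for another reason.

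**The case against.** **The high-side trigger is deliberate and reasonable.** Section 1 lists hyperglycemia and insulin resistance among the adverse effects of recombinant growth hormone. Section 1.1 makes insulin sensitivity and diabetic control the purpose of the study. Section 3.3.3 sets a withdrawal limit at fasting glucose above 300 mg/dL, for which a call at 250 mg/dL is an early warning. No low-side stopping rule exists for a low-side call to feed. This stands: a reader might infer that the one-sided rule has no rationale, and the documents do not support that. The rationale explains why highs are included. It does not explain why lows are left out.

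**Lows are already captured.** They go into both the diary and the meter. Under Section 3.5.2.1 subjects may volunteer adverse events, and nothing bars contact between visits. This also stands: a reader might infer that hypoglycemia data are lost, and they are not. The remaining point is promptness only.

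**The missing instruction may be in a document that is not shown.** Meter and diary instructions are given out at Visit 2, and those instructions, the consent pages, Appendix 1 and Section 6 are not available here. Any of them may tell subjects to call for a low. This limits the point to the visible protocol. If such an instruction exists, aligning the protocol with it costs almost nothing.

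**The size of the problem is unknown.** This stands as well. One could count up to 4 × 31 = 124 scheduled readings in a 31-day interval, or average the nominal visit spacing on drug as (7² + 21² + 28² + 28²) / (2 × 84) = 2058 / 168 = 12.25 days to the next visit. The first figure counts all readings, not lows. The second describes the calendar, not actual delay. Neither measures harm.

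**Conclusion.** The point holds as a minor patient-safety improvement. The protocol fixes a call rule in five places, on one side only, for subjects whose treatment and possible dose changes make the other side foreseeable. The only size the documents support is the scheduled interval between site reviews, which is at most 31 days on or off study drug. The number of episodes affected cannot be computed because no hypoglycemia rate is given.

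The conclusion assumes that no unseen instruction already covers lows and that a subject might not call unprompted.

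Two stronger readings should be resisted:
- A reader might infer that eligibility screens on episode counts alone. Criterion 8 also excludes on hospitalization or emergency room visits for poor glycemic control, so part of the higher-risk group is removed.
- A reader might infer a demonstrated delay in serious event reporting. That effect is conditional on a low being serious and not reaching the site sooner. The convulsion example in Section 3.5.2.2 is generic and is not tied to hypoglycemia.

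The sample size and the primary analysis are unaffected.

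**What to change.** Use one wording in Section 3.5.2.3.7 and in the Visit 3, Visit 4, Visits 5/6 and Visit 7 lists: subjects phone the site for any home reading above 250 mg/dL, for any hypoglycemic episode, or for any home reading below a stated value. The medical monitor should set that value before enrollment, and it should be written into the protocol. The documents give no figure, so none is proposed here. The clause on hypoglycemic episodes can be adopted at once, without waiting for the value.

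Keep the wording at Visit 7. Glucose-lowering doses changed during treatment may continue after study drug stops, and the next visit is 25 to 31 days later.

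The cost is one clause in five places, one threshold to agree, and extra calls to sites. The number of calls is unknown, and it would include calls for mild episodes.
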